**Methods/Design:**

Families will be randomised to receive either Baby Triple P for Preterm infants or Care as Usual (CAU). Baby Triple P for Preterm infants involves 4 × 2 hr group sessions at the hospital plus 4 × 30 min telephone consultations soon after transfer (42 weeks C.A.). After discharge participants will be linked to community based Triple P and intervention maintenance up to 24 months C.A. Assessments will be: baseline, post-intervention (6 weeks C.A.), at 12 and 24 months C.A. The primary outcome measure is the Infant Toddler Social & Emotional Assessment (ITSEA) at 24 months C.A. Child behavioural and emotional problems will be coded using the mother-toddler version of the Family Observation Schedule at 24 months C.A. Secondary outcome will be the Bayley Scales of Infant and Toddler Development (BSID III) cognitive development, language and motor abilities. Proximal targets of parenting style, parental self-efficacy, parental mental health, parental adjustment, parent-infant attachment, couple relationship satisfaction and couple communication will also be assessed. Our sample size based on the ITSEA, has 80% power, predicted effect size of 0.33 and an 85% retention rate, requires 165 families are required in each group (total sample of 330 families).

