**Consort flow chart for Baby Triple P for preterm infants.**

The primary hypotheses to be tested are:H^1^ Children whose parent/s participated in Baby Triple P for Preterm infants will score significantly higher on measures of behavioural and emotional adjustment at 24 months C.A. than children whose parents received CAU.H^2^ Children whose parent/s participated in Baby Triple P for Preterm infants will score significantly higher on measures of cognitive, language and motor development (BSID III) than children whose parents received CAU at 24 months C.A.

The secondary hypotheses to be tested are:H^3^ Parents who participated in Baby Triple P for Preterm infants will have significantly better parent and couple outcomes than parents who received CAU (including parenting style, parental self-efficacy, parental mental health and relationship satisfaction). Whether these proximal factors are important in mediating the treatment effect on primary and secondary child outcomes at 24 months C.A. will be tested.

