### Sample size

The sample size needs to be sufficient to provide reliable evidence about whether family functioning is sufficiently impacted by the Baby Triple P for Preterm infants intervention to improve the primary outcome of child behavioural and emotional problems. A clinically important difference in child behavioural and emotional problems is considered to be a standardised effect size of 0.33 on the ITSEA [49]. This is a conservative estimate of the expected effect size observed in past RCTs of Triple P [36]. With a type-1 (alpha) level of 0.05, and 80% power, a total of 140 per group are required for analysis. Based on our experience, the expected retention rate is > 85% so that 330 families (n = 165 in each group) will be recruited to allow for attrition. As babies of multiple births cannot be considered independent, the unit of randomisation is family (or delivery), and the total number of babies recruited will depend on the number of multiple births. A total of ~675 families of preterm infants born at <32 weeks who survive to term equivalent are admitted to RBWH and MMH combined over the proposed 3 year recruitment period. Allowing for the estimated retention rate of 50% of those eligible, the feasibility is high of recruitment of a sufficient sample of at least 330 of the eligible 338 families to be studied at 24 months C.A.

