### Child outcomes

Primary Outcome Child Behavioural and Emotional Problems:*Infant Toddler Social & Emotional Assessment* [49,51] (ITSEA); will be assessed at 12 and 24 months C.A: This is a primary outcome measure of the study (at 24 months C.A.). The ITSEA is a 165-item parent-report questionnaire to assess social-emotional problems/competencies in the domains of behavioural dysregulation; externalising behaviour; internalising behaviour, and competence Items are presented as statements e.g. “Your child is restless and can’t sit still” and rated on a 3-point scale 0 (not true/rarely) 1 (somewhat true/sometimes) 2 (very true/often). This study will utilise only the externalizing, internalizing and dysregulation subscales. The ITSEA has established concurrent validity, strong test-retest reliability (α = .75-.91) and good internal reliability for each subscale (α = .86 for dysregulation, α = .87 for externalising, α = .85 for internalising, and α = .89 for competence) [49,51].*Observation of mother-child interaction* over 15-minutes will be video-recorded (at 24 months C.A.) during a series of structured tasks to corroborate parent reported data on child behavioural and emotional problems. For example child behaviours coded for are non-compliance, complaint, aversive demands and positive contact. Observations will be conducted in the hospital and will consist of four timed segments: 3 minutes of free play with toys provided, 5 minutes of a compliance task where the parent instructs the child to work with them on a paper and crayon task involving the parent giving simple instructions to the child; 5 minutes where the parent is made ‘busy’ by completing a questionnaire, and 2 minutes of a second compliance task in which the parent instructs the child to pack up the toys. Steps will be taken to reduce the effects of reactivity by positioning the camera as far away as is reasonable and having the researcher leave the room between segments. Coding of the observations will be done by a researcher and trained research assistants using the Family Observation Schedule (FOS [52];which has demonstrated reliability and discriminant validity [15,48,53,54]. The FOS is a microanalytic coding system in which the presence or absence of particular behaviours of both the child are scored in consecutive 10-s intervals. Where the child has a physical disability the tasks will be modified.*Observation of mother-child interaction (6 weeks and 12 months CA).* Participants living within 100 kilometres ‘*as the crow flies’* from Brisbane, will complete a video-recorded mother-infant observation conducted in the mother’s home at 6 weeks and 12 months CA. At 6 weeks CA the researcher will instruct the mother to position herself face-to-face with the infant. The mother will then be instructed to interact the way she normally would with her infant, and to attend to any care the infant may require, for example, feeding. The observation will be recorded for 15-minutes. At 12 months CA the researcher will again instruct the mother to interact the way she normally would with her child, this time through a series of 5 segments: 2-minute interaction with a pop-up toy; a limited physical availability task involving a 3-minute telephone call from the researcher to the mother; 4-minute interaction with a set of blocks; 4-minute interaction with a puzzle; 6-minute interaction with a train set. The mother will be instructed to pack up each toy between segments. The observation will be recorded for 20-minutes. Both observations will be coded using the Emotional Availability Scales (EA Scales) [55] by two independent coders blind to group allocation. The measure assesses the quality of the mother-infant relationship across four caregiver scales (sensitivity, structuring, nonintrusiveness and nonhostility) and two child scales (responsiveness and involvement). The scale has high inter-rater reliability: sensitivity (.89), structuring (.91), nonintrusiveness (.86), nonhostility (.76), responsiveness (.88) and involvement (.87) [56].*Baby Behaviour Inventory* (BBI): will be assessed at 6 weeks post and 12 months C.A. The BBI is a 14-item measure of problematic baby behaviour with three scales: an intensity scale, a problem scale and a confidence scale. Each item describes an infant behaviour e.g. “Baby waking more than four times per night”. For the intensity scale parents indicate how often this behaviour occurs with their baby on a 5 point scale 1 (Never) 2 (Seldom) 3 (Sometimes) 4 (Often) 5 (Always). Parents then indicate if they experience the behaviour as a problem (yes/no) (problem scale) and if so then they rate their level of confidence in dealing with the problem on a 5 point scale 1 (Never confident) 2 (Sometimes confident) 3 (Confident) 4 (Very confident) 5 (Extremely confident). The BBI has reasonable internal consistency (α = .84 for overall intensity scale) and test-retest reliability (*r* = .70, .59 and .57 for the intensity, problem and confidence subscales respectively) and demonstrated construct validity [40].

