
### Analyses

Analysis will follow standard principles for randomised controlled trials using 2-group comparisons performed using all subjects for whom outcome data are available, on an intention-to-treat basis. The experimental unit is a family. The effect of clustering for children in multiple births will be partitioned from the experimental error, which will be estimated from the between family variability. Up to 50% of eligible families may not consent or alternatively, be back-transferred to regional hospitals before an approach can be made, and a further 15% may be lost to follow-up at 2 years. Consequential threats to external and internal validity will be checked using baseline and descriptive information for eligible families. Imputation techniques will be used to avoid bias which may be a consequence of non-ignorable missing data during follow-up. All data analyses were performed using STATA 10.0 (Statacorp 2007).

The primary endpoint at 24 months C.A. is the child behavioural and emotional problems as measured on the ITSEA and the mother-toddler observation. This comparison will be between treatment groups using general linear models, with terms included for stratification and important confounding variables, such as the extent of brain injury and socio-demographic variables. Secondary analyses will use similar methods to compare the outcomes between groups for the additional outcomes (cognition, language etc.). For dichotomous outcomes, comparison will be by chi-square tests and multiple logistic regression. Where continuous data exhibit substantial skewness not overcome by transformation, non-parametric methods (Mann–Whitney *U* test) will be used for simple comparisons. Further analysis will be performed using latent growth modelling (LGM) [78,79] as it provides simultaneous analysis of time points and can incorporate latent measures corrected for measurement error [80]. The added-growth LGM used in evaluating the efficacy of Baby Triple P for Preterm infants tests the extent to which the intervention alters the trajectory of the target behaviour [79]. The models may incorporate main effects of time-independent and dependent covariates (e.g. control variables) on trajectories, as well as interactions of such measures with intervention effects [78,79]. The models express the expected change in dependent variables as a function of exposure to the intervention (e.g. Baby Triple P for preterm infants versus Control).

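### The protocol gives conflicting primary endpoints and names no primary ITSEA score, so its single-test alpha and power cannot be tied to one defined analysis

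*Protocol article*

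**What the plan says.** Four places in the protocol article assign a status to the 24-month child measures.

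- **Abstract, Methods/Design:** "The primary outcome measure is the Infant Toddler Social & Emotional Assessment (ITSEA) at 24 months C.A", followed by "Secondary outcome will be the Bayley Scales of Infant and Toddler Development (BSID III) cognitive development, language and motor abilities".
- **Methods, list of primary hypotheses:** H1 says that intervention children "will score significantly higher on measures of behavioural and emotional adjustment at 24 months C.A". H2, under the same heading, says that they "will score significantly higher on measures of cognitive, language and motor development (BSID III) than children whose parents received CAU".
- **Child outcomes:** the ITSEA is described as one primary measure (indefinite article), and the 24-month video observation is there to back up what parents report. On scoring: "This study will utilise only the externalizing, internalizing and dysregulation subscales". No total, composite or lead subscale is named. At least four child codes are listed as examples for the observation, without a summary score.
- **Analyses:** "The primary endpoint at 24 months C.A. is the child behavioural and emotional problems as measured on the ITSEA and the mother-toddler observation". Cognition and language come under secondary analyses.

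The Sample size section plans for one standardised effect of 0.33 on the ITSEA, without saying which score: "With a type-1 (alpha) level of 0.05, and 80% power, a total of 140 per group are required for analysis".

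**The concern.** BSID III is secondary in the abstract and in Analyses but belongs to a primary hypothesis in Methods. The observation is supporting evidence in one section and half of the primary endpoint in another. An analysis plan that is not shown could add a testing rule, but it could not make these statements agree.

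The choice can change the trial's conclusion. The ITSEA is completed by parents who know their allocation, while coders of the observation and BSID III assessors are masked (Blinding section). Two plausible results show the problem:

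- **ITSEA positive, masked observation null:** a success by the abstract, undetermined by the Analyses section.
- **ITSEA null, BSID III positive:** a failure by the abstract, yet support for a primary hypothesis by the Methods list.

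If this stays open, the primary result can be settled after the data are seen. In addition, one alpha and one power figure are quoted for an endpoint that consists of at least three scores.

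**Working it through.** **Inputs.** From Sample size: alpha 0.05, power 80%, effect d = 0.33, n = 140 per group analysed, retention 85%, 165 per group recruited. From Child outcomes: three ITSEA subscales. Assumptions: two-sided test (sidedness is not stated; one-sided would need 114 per group, far from 140); a true effect of 0.33 on every score in the power calculations; equal correlation rho between scores, varied from 0 to 0.7 because the document gives none.

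**1. The plan's own figure, one score.** Power = Φ(d·√(n/2) − z).
- d·√(n/2) = 0.33 × √70 = 2.761.
- Φ(2.761 − 1.960) = Φ(0.801) = 78.8% (t-test 78.6%).
- The n for exactly 80% is 145 per group, so 140 costs about one point of power. That is a rounding matter and not part of this point.
- Attrition: 140 / 0.85 = 164.7, hence 165, as stated.

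The stated design is therefore sound for one named score or composite with that effect, or for the first test in a fixed order.

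**2. Any one of several unadjusted scores counts.** With independent scores, the false-positive chance is 1 − 0.95^m.
- Three subscales: 1 − 0.95³ = 14.3%. Simulated with correlation: 13.6% (rho 0.3), 12.6% (0.5), 10.9% (0.7).
- Three subscales plus one observation score: 1 − 0.95⁴ = 18.5%, falling to about 13% at rho 0.7.

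**3. All three subscales must succeed, each at 0.05.**
- Independent: 0.788³ = 49%. Simulated: 55% (rho 0.3), 59% (0.5), 64% (0.7).

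**4. Bonferroni over three subscales (alpha 0.05/3 = 0.0167, z = 2.394).**
- Power for one given subscale: Φ(2.761 − 2.394) = Φ(0.367) = 64.3%. Reaching 80% would take 193 per group, or 228 recruited.
- Power for at least one of three: 1 − (1 − 0.643)³ = 95.5% if independent, and 81.3% at rho 0.7.

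| Success rule | False-positive chance | Power at 140 per group |
|---|---|---|
| One named score, or first in a fixed order | 5% | 79% |
| Any of three, unadjusted | 11% to 14% | not needed here |
| All three at 0.05 | at most 5% | 49% to 64% |
| Bonferroni over three | at most 5% | 64% for one given subscale; 81% to 95.5% for at least one |

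**The case against.** The strongest reply is that the article never says every score is tested at 0.05, nor that any single result is enough. Alpha appears once, in the sample size, for one effect on the ITSEA. The choice of score and the handling of multiplicity are commonly left to a fuller document. This stands: the lack of a multiplicity rule is not the finding, and the error rates above are conditional.

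Three stronger readings are tempting but unsupported.

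- **The stated alpha and power are wrong.** A reader might infer this from the number of scores. Both figures reproduce for one score, and even with Bonferroni the power to succeed on at least one subscale stays above 80% if all three true effects are 0.33. The 64% figure answers a different question (one given subscale) and should not be paired with an any-of-several error rate.
- **Seven primary tests, with up to 30% error.** This adds three BSID III scores to three subscales and one observation score. The abstract and Analyses both class BSID III as secondary, and the hypotheses list itself distinguishes primary from secondary child outcomes. The placement of H2 looks like a labelling slip.
- **H1 predicts harm.** H1 expects higher scores while the retained ITSEA subscales are problem scales. But H1 speaks of adjustment, where higher reads naturally as better, and the outcome is called problems elsewhere. The direction of a two-sided test is unaffected, so this is wording only.

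The reply does not remove the contradiction between sections or the lack of a named ITSEA score behind the sample size.

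**Conclusion.** The point holds as an internal contradiction. The status of BSID III and of the observation changes between sections, and the single-test calculation cannot be attached to one defined primary analysis. The planned figures are right for one pre-specified ITSEA score. Under other rules that the text leaves open, the false-positive chance could rise to about 11% to 14% (up to 18.5% with an observation score), or power could fall to about 49% to 64%. These sizes rest on the assumed two-sided test, equal correlations of 0 to 0.7 and, for power, a true effect of 0.33 on each score. The document does not show that any of those rules is intended. Correction is still needed because the same data could lead to different primary conclusions depending on the section followed.

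**What to change.** Use one definition in the abstract, the hypotheses list, Sample size, Child outcomes and Analyses.

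1. Make the ITSEA at 24 months corrected age the sole primary endpoint, in one of two ways:
   - one pre-specified score, either a named lead subscale or the mean of the three standardised subscales, tested at two-sided 0.05; or
   - the three subscales with Holm at overall two-sided 0.05, with power restated for that rule.
2. Make the masked observation (one pre-specified score) and BSID III secondary everywhere, and move H2 to the secondary hypotheses.
3. Say in Sample size which ITSEA score or rule the effect of 0.33 refers to.
4. Reword H1 as lower ITSEA problem scores.

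The cost is wording, to be settled before unblinding; no extra data or families are needed. With one score, power stays at about 79%. With Holm, the stated power for a single subscale is less favourable (about 64% at its first step), while the chance of succeeding on at least one subscale is the same as under Bonferroni, about 81% to 95.5% if all three true effects are 0.33.
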